### Trial Management

The day-to-day management of the study will be undertaken by a clinical research fellow. Support will be provided by the co-investigators who will meet on an at least quarterly basis to discuss any matters that arise will the trial. The intervention is low risk and as such there will be no data monitoring committee. As this is not a clinical trial of an investigational medicinal product (CTIMP), there is no requirement for Medicines and Healthcare products Regulatory Agency (MHRA) approval or trial registration.

### Quality assurance

The Study will be conducted by trained personnel following departmental Standard Operating Procedures with Quality Control. Standardised delivery of the interventions will be assured by all interventions being delivered by one clinical research fellow using a computerised intervention. Source data verification will be performed by monitors from the University of Oxford Clinical Trials and Research Governance department.

### Sample size and rate of recruitment

The study has 80% power at the 5% level of significance to detect a difference of 30,000 total accelerometer counts per day of physical activity between the groups with a sample size of 46 per cell, assuming the estimated total counts per day is mean (SD) 275,400 (101,600) minutes[31]. This equates to 92 participants per arm of the study. We will randomise a total of 200 subjects to allow for a small drop-out rate. We expect retention of study participants to be high because of the short duration and non-invasiveness of the study. Recruitment is anticipated to continue for one year.

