**Methods/Design:**

In a 2 × 2 factorial design participants are allocated at random to a personalised 10-year CVD risk estimate or numerical CVD risk factor values (systolic blood pressure, LDL cholesterol and fasting glucose) and, simultaneously, to receive a brief lifestyle advice intervention targeting physical activity, diet and smoking cessation or not. We aim to recruit 200 participants from Oxfordshire primary care practices. Eligibility criteria include adults age 40–70 years, estimated 10-year CVD risk ≥20%, ability to read and write English, no known CVD and no physical disability or other condition reducing the ability to walk. Primary outcome is physical activity measured by ActiGraph accelerometer with biochemical, anthropometrical and psychological measures as additional outcomes. Primary analysis is between group physical activity differences at one month powered to detect a difference of 30,000 total counts per day of physical activity between the groups. Additional analyses will seek to further elucidate the relationship between the provision of risk information, and intention to change behaviour and to determine the impact of both interventions on clinical and anthropometrical measures including fasting and 2 hour plasma glucose, fructosamine, serum cotinine, plasma vitamin C, body fat percentage and blood pressure.

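### The stated 80% power for 30,000 counts/day does not follow from the protocol's own inputs, which give about 51–52%

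*Protocol article*

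**What the plan says.** The section on sample size and rate of recruitment gives all the ingredients of a two-group power calculation:

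- Power, significance level and target effect: "The study has 80% power at the 5% level of significance to detect a difference of 30,000 total accelerometer counts per day", as a difference between the groups. Sidedness is not given.
- Variability: "assuming the estimated total counts per day is mean (SD) 275,400 (101,600) minutes".
- Size: "with a sample size of 46 per cell", followed by "This equates to 92 participants per arm of the study".
- A total of 200 are to be randomised, to cover a small drop-out.

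The abstract repeats the claim. It defines the primary analysis as the between-group difference at one month, "powered to detect a difference of 30,000 total counts per day of physical activity between the groups".

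The statistical analysis section plans a Poisson or negative binomial generalised linear model for the accelerometer data, reported as rate ratios. It mentions no baseline term for that model. Participants without enough valid wear time in each recording period are excluded, and missing accelerometer data are not imputed.

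**The concern.** The target difference is about 0.3 of the SD (30,000 / 101,600 = 0.295). An effect of that size normally needs well over 150 per group for 80% power, so 92 per arm looked too small by about a factor of two.

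If the 80% is wrong, a true effect of the planned size would be missed about half the time. A reader of a null result would nevertheless take it to come from a trial with 80% power. The study design section presents the trial as a pilot for a larger one, so the error could also carry into the next sample size calculation.

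**Working it through.** **Inputs**, all from the sample size section: difference d = 30,000; SD s = 101,600; α = 0.05, taken as two-sided; n = 92 per arm (2 × 46); equal allocation.

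**1. The plan's figure: power at 92 per arm**

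- SE = s × √(2/n) = 101,600 × √(2/92) = 14,980
- d / SE = 30,000 / 14,980 = 2.003
- Power = Φ(2.003 − 1.960) = 51.7%; the noncentral t gives 51.3%

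The stated 80% is not reproduced.

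**2. Number needed for 80%**

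- n per arm = 2 × [s × (1.960 + 0.842) / d]² = 2 × (101,600 × 2.802 / 30,000)² = 2 × 90.05 = 180.1, so 181
- The t-test solution is 181.01, so 182
- Total evaluable: 362–364, against 184 (4 × 46) in the plan

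**3. Difference detectable with 80% power at 92 per arm**

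- 2.802 × 14,980 ≈ 42,000 (41,968 unrounded; 42,191 by t-test)
- The Discussion equates 100,000 counts with about 30 minutes of brisk walking. On that scale 30,000 is about 9 minutes a day (0.30 × 30) and 42,000 about 12.6 minutes (0.42 × 30).

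**4. Readings that might rescue the 80%**

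| Reading | Power for 30,000 |
|---|---|
| 92 per arm, two-sided | 51.7% (t: 51.3%) |
| 92 per arm, one-sided 5% | 64.0% (t: 63.7%) |
| 100 per arm (all 200 analysed), two-sided | 55.1% (t: 54.7%) |
| 100 per arm, one-sided 5% | 67.1% (t: 66.9%) |
| Log or rate-ratio scale, 92 per arm, two-sided | about 48–59% |
| Cell against cell, 46 v 46, two-sided | 29.3% (t: 28.8%) |

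The log-scale row approximates the planned rate-ratio analysis. It uses a coefficient of variation of 101,600 / 275,400 = 0.369 and a ratio of 305,400 / 275,400 = 1.109 or 275,400 / 245,400 = 1.122. The range depends on which group has the stated mean and on how the log-scale SD is approximated.

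**5. What baseline adjustment would have to deliver**

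- SD needed for 80% at 92 per arm: 30,000 / (2.802 × √(2/92)) ≈ 72,600 (t-based: 72,243)
- Ratio to the stated SD, squared: (72,243 / 101,600)² = 0.506
- ANCOVA: 1 − r² = 0.506, so r ≈ 0.70
- Change scores: 2(1 − r) = 0.506, so r ≈ 0.75

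**6. Possible origin (inference only)**

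Two slips would give the planned size. The per-arm requirement of 181 or 182 divided by four cells rounds up to 46, as if it were the trial total. A one-sample or paired t-test with the same d and s needs 91.96, so 92. Each loses a factor of two. The article names no formula, and the finding does not depend on which occurred.

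**The case against.** The best defence is baseline adjustment. Accelerometry is collected before randomisation, valid wear is required in both recording periods, and the statistical analysis section says that change from baseline to one month will be analysed. With ANCOVA and a correlation of 0.70, power at 92 per arm is 79.7%; with change scores and 0.75 it is 80.4%. An analysis plan not shown here could specify this. It therefore stands that 51–52% is the power of an unadjusted comparison, and not necessarily of the analysis finally run.

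This does not support the stated figure. The sentence on change follows one about demographic, clinical and biochemical variables, while accelerometer counts have their own model with no baseline term. The abstract sets the primary analysis as the between-group difference at one month. The SD is printed beside a mean of 275,400, so it is the SD of the activity level and not of change. No correlation appears anywhere.

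Four smaller points:

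- The calculation is for a difference in means, whereas the planned model gives rate ratios. That is fair, and 51–52% should not be read as exact for that model, but the log-scale range of about 48–59% leads to the same conclusion.
- The trial is a pilot. That tempers how a null result might be read, but it does not excuse an explicit 80% claim for the primary analysis.
- The 29% for single cells is peripheral, because the power statement concerns arms of 92.
- The wrong unit has no numerical consequence.

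**Conclusion.** The concern holds. On the article's own inputs, power for 30,000 counts/day is about 51–52%, not 80%. The trial would need about twice the planned number per arm (181–182 against 92) to meet its claim, or must accept a detectable difference of about 42,000.

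This rests on a two-sided 5% test, an unadjusted comparison of two independent groups, pooling over the other factor, and 92 evaluable per arm. Pooling is the reading of group size most favourable to the plan. The figure falls further if exclusions for insufficient wear and other losses exceed the 16 spare participants (200 − 184). Only a baseline correlation of about 0.70–0.75, used in the primary analysis, would restore 80%, and the article states neither the correlation nor that use.

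**What to change.** Keep 200 participants and correct the sample size section in one of two ways.

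- **No baseline adjustment assumed.** Replace the power sentence with, for example: *With 92 evaluable participants per arm, the trial has 80% power at the two-sided 5% level to detect a difference of about 42,000 counts/day, and about 51% power for 30,000 counts/day, without adjustment for baseline.*
- **Baseline adjustment was assumed.** State the correlation and its source (about 0.70 is needed for ANCOVA, about 0.75 for change scores), and commit the primary accelerometer analysis to that adjustment.

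In either case, keep the condition that the numbers are evaluable participants, state the sidedness of the test, change the unit of the mean and SD from minutes to counts per day, and carry the corrected statement into the abstract.

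The cost is wording only. No extra participants are needed, but the stated power or detectable difference becomes less favourable unless the second route can be justified.

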### Statistical analysis

Only data for participants who record at least 500 min/day of activity for at least 4 days during each 7 day period will be analysed. Data will be presented in terms of total body movement (counts·day^-1^), which is an indicator of the total volume of physical activity, and time (minutes·day^-1^) spent at different activity intensity categories averaged per day over the measurement period. Intensity thresholds for sedentary, light, moderate, vigorous and very vigorous intensity physical activity will be defined according to Freedson *et al *and Ekelund *et al*[32,33]. We will also determine the average number of 5- and 10-min bouts of sustained physical activity at moderate or greater intensity allowing 1 min to drop below the threshold for moderate activity in each 5-min bout. We will calculate the proportion of participants in each group accumulating 30 min or more per day of moderate or greater intensity physical activity, the current UK recommendation for physical activity[28]. Data reduction, cleaning, and analyses of accelerometer data will be performed using appropriate software (MAHUffe; see ). Generalized linear model (Poisson distribution or Negative Binomial distribution) as appropriate will be used and estimates of Rate Ratios along with 95% confidence interval will be presented.

Demographic, clinical and biochemical study variables will be summarized using number (percentage) and measures of location and dispersion as appropriate. The change in the study parameters from baseline to one month will be analysed and inference drawn using appropriate statistical methods, keeping in mind the nature of distributions of the study variables. Analysis will be by intention to treat (ITT).

To analyse the highly skewed EQ-5D scores, appropriate non-parametric technique will be used. Other questionnaire data will be analysed using appropriate non-parametric tests to compare average scores as well as distribution of scores in each group. Should a questionnaire generate only a finite number of scores, the data will then be considered polytomous and suitable statistical techniques will be used to analyse any such data.

Any missing biochemical data will be imputed using the Last Observation Carried Forward technique. Any missing accelerometer data however, will not be imputed for.

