### Telephone contact

Once a participant has expressed interest in taking part in the study by returning a reply slip in a prepaid envelope or by emailing or telephoning the research team a researcher obtains verbal consent and arranges a date and time for visit 1. ActiGraph accelerometers (model GT1M, Manufacturing Technology, Fort Walton Beach, FL) are then mailed to recruited participants approximately one week prior to visit 1 in order to reduce the number of visits and to reduce the potential effect of measurement on baseline physical activity. Simple instructions on how to use the device are provided and participants are asked to wear the accelerometer for seven days in total over a mixture of week and weekend days. Accelerometers are worn on an elastic belt around the waist and are removed for sleep, bathing, showering and swimming.

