### Baseline assessment

Baseline clinical assessment is conducted by a clinical researcher and research nurses prior to randomisation in a clinical research unit. Written informed consent is collected at this visit. Medical history, demographic details, age at leaving school and electoral ward are collected. A 75 mg anhydrous oral glucose tolerance test (0 and 120 minute glucose sampling) is conducted and fasting blood samples taken for total, LDL and HDL cholesterol, triglycerides, HbA1c, serum cotinine, plasma vitamin C and fructosamine assessment. Anthropometric measurements are taken (resting blood pressure, height, weight, waist circumference, body fat percentage). Smoking status, current medication and self-reported alcohol intake is recorded. An ECG is performed. A booklet of questionnaires comprising the short-form Spielberger anxiety inventory[20], EQ5D questionnaire[21], Illness perception questionnaire, adapted Lerman cancer worry scale[22], psychological impact questionnaire, Recent Physical Activity Questionnaire (RPAQ) and A Fear-Avoidance Beliefs Questionnaire (FAB) is completed by each participant. Once these data have been collected the participant is randomised and any interventions delivered at this study visit.

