### Outcome assessment

Follow-up at four weeks occurs for all measures including oral glucose tolerance test, blood samples, anthropometric measurements, smoking status, current medication, alcohol intake and questionnaires with the addition of a recall of risk information questionnaire. Physical activity is again measured by accelerometer for seven days in the week before the second study visit.

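### The primary comparison is a two-week completers analysis described as ITT: it discards valid one-month outcomes, and the sample size does not mention invalid wear

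*Protocol article*

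**What the plan says.** All of the following is in the protocol article.

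- Analysis set (Statistical analysis), as the opening rule of that section: "Only data for participants who record at least 500 min/day of activity for at least 4 days during each 7 day period" enter it.
- Principle, two paragraphs' scope apart in the same section: "Analysis will be by intention to treat (ITT").
- Missing data (end of that section): "Any missing accelerometer data however, will not be imputed for". Missing biochemical values, by contrast, are carried forward.
- Baseline wear (Telephone contact): the devices are "mailed to recruited participants approximately one week prior to visit 1".
- Randomisation (Baseline assessment): "Once these data have been collected the participant is randomised and any interventions delivered at this study visit".
- Follow-up wear (Outcome assessment): "Physical activity is again measured by accelerometer for seven days in the week before the second study visit".
- Sample size (Sample size and rate of recruitment): 46 per cell, 92 per arm, 184 in all; then "We will randomise a total of 200 subjects to allow for a small drop-out rate".

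The abstract gives the primary outcome as accelerometer-measured activity and the primary analysis as the between-group difference at one month.

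**The concern.** A participant must pass the wear rule in both weeks to be counted, and nobody who fails is imputed. For the primary outcome this is not what a reader will understand by ITT.

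The two halves of the rule do different harm:

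- **Follow-up week.** Wear in this week comes after the participant has received, or not received, a risk estimate and lifestyle advice. The participant knows which. If the interventions alter willingness to wear the device, and wear is related to activity, the participants left in each arm are no longer comparable.
- **Baseline week.** Wear in this week cannot depend on allocation. Requiring it removes people whose one-month outcome was observed and valid, for a contrast that the abstract defines at one month.

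The sample size is inflated for drop-out alone, so any loss from invalid wear comes out of the same small margin.

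**Working it through.** **1. Order of events.** Baseline wear, then visit 1 with randomisation and intervention, then follow-up wear, then visit 2. The baseline condition is therefore pre-randomisation and the follow-up condition post-intervention.

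**2. The allowance.** 1 − 184/200 = 8% total loss. To keep 184 with no drop-out at all, the share valid in each week must be at least √(184/200) = 95.9% if the weeks are independent, or 92% if the same people fail both weeks.

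**3. The plan's own power figure.** Inputs: difference 30,000 counts/day, SD 101,600, 92 per arm, 5% level. The sidedness is not stated; two-sided is assumed. The noncentrality is 30,000 / (101,600 × √(2/92)) = 2.00, which gives 51% power by the noncentral t. The stated 80% is not reproduced. It would need an SD of about 72,600: 30,000 / (2.802 × √(2/92)) = 72,627 by the normal formula. That gap is a separate matter, so the effect of the wear rule is shown on both SDs.

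**4. Loss under an assumed 90% valid in each week.** The documents give no validity rate; 90% is an illustration and drop-out is set to zero.

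- Independent weeks: 200 × 0.90 × 0.90 = 162, or 81 per arm.
- Full overlap of failures: 200 × 0.90 = 180, or 90 per arm.
- Follow-up rule only: 180, whatever the overlap.

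With independent weeks, the baseline condition alone discards 180 − 162 = 18 valid one-month outcomes.

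| Analysed per arm | Power, SD 101,600 | Power, SD 72,627 |
|---|---|---|
| 92 (planned) | 51.3% | 79.6% |
| 90 (full overlap, or follow-up rule only) | 50.4% | 78.7% |
| 81 (both weeks, independent) | 46.3% | 74.3% |

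All entries are two-sided noncentral t. Going from 92 to 81 per arm costs about 5 points on either SD. About 4 of these come from the baseline condition (90 to 81).

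**5. Possible selection bias.** If excluded people differ from completers by g counts/day in both arms, and exclusion differs between arms by Δ, the completers' difference is shifted by Δ × g. Neither quantity is in the documents. With Δ = 0.10 assumed:

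- g = 50,000: shift 5,000, which is 17% of the 30,000 target.
- g = 100,000: shift 10,000, which is 33%.

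The sign depends on which arm loses more of its less active people. If the interventions encourage wear, the control arm loses more, its completers look more active, and a true benefit is pulled towards zero. If the intervention arm loses more, the shift goes the other way.

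**The case against.** The case for the plan has several sound parts.

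- **A minimum-wear rule is reasonable.** A sparse record is not a usable outcome. This stands, and the fix keeps the rule.
- **The rule is disclosed, and the ITT sentence closes a paragraph on clinical variables and change from baseline.** Analysis as allocated among those with outcomes is often called ITT. But the sentence carries no restriction, and a reader will apply it to the primary outcome. The label needs correcting.
- **Losses may be small.** The article expects high retention because the study is short and non-invasive, and people who wear the device well in one week probably do so in the other. That is why 162 is the low end of a range reaching 180. Up to 8% total loss is absorbed.
- **This is a pilot, and imputation detail belongs in an analysis plan that is not shown.** This is fair for the choice of method. It does not cover the both-weeks exclusion, the ITT label and the bar on imputation, which the article itself fixes.

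Some stronger readings are tempting and are not supported:

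- A reader might infer that the wear rule takes power from 80% down to 46%. Most of that distance is already there at 92 per arm with the printed SD.
- A reader might infer that both conditions cause selection bias. The baseline condition cannot, because it precedes randomisation.
- A reader might take 500 min/day of activity as selection on the outcome itself. The same paragraph lists sedentary time among the activity categories, so recorded wear time is the natural meaning. This is a wording point.
- A reader might conclude that the bias would produce a false positive. Its direction is unknown, and the most obvious mechanism points towards the null.

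**Conclusion.** The point holds in this form. The primary one-month comparison, as fixed in the article, is a completers analysis over two weeks and should not be described as ITT. The baseline condition costs precision without a gain in validity. The follow-up condition leaves room for selection bias, and the article describes no analysis that would show its size.

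The power cost is about 5 points if 90% are valid in each week and the weeks are independent, and about 1 point if the same people fail both. Drop-out would add to either figure. These sizes rest on an assumed validity rate, and the bias figures on an assumed difference in exclusion and an assumed activity gap. What the documents themselves establish is the conflict between the rule and the label, the discarding of valid outcomes, and an 8% allowance that does not mention invalid wear.

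**What to change.** 1. Word the rule as at least 500 minutes of recorded wear time per day on at least 4 days, and apply it to the follow-up week only.
2. Analyse all randomised participants with a valid follow-up week, as allocated. Where baseline counts are a covariate, keep those with an invalid baseline week by mean imputation or a missing-data indicator. Either is acceptable here because baseline wear precedes randomisation.
3. Stop calling the both-weeks set ITT. Keep it as a labelled completers sensitivity analysis.
4. Add a sensitivity analysis for missing follow-up counts, using multiple imputation with a delta shift. Imputation as the primary analysis is debatable, since it would not remove bias that comes from unmeasured motivation.
5. Report the number excluded, by week and by arm.
6. State in the sample size section whether the 8% allowance is meant to cover invalid wear as well as drop-out.

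The cost is a change of wording and some extra analysis, with some participants carrying an imputed baseline value. No new visits or data are needed. The changes should be settled before outcome data are seen.

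### The plan permits a Poisson model for total accelerometer counts that its own SD rules out with model-based errors, and it reports only a rate ratio although the trial is sized on a difference

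*Protocol article*

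**What the plan says.** The Abstract (Methods/Design) names accelerometer-measured physical activity as the primary outcome and states: "Primary analysis is between group physical activity differences at one month powered to detect a difference of 30,000 total counts per day".

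The section on sample size and rate of recruitment claims "80% power at the 5% level of significance". The target is the same 30,000 counts/day, and each of the four cells is to hold 46 people. The planning values are worded as follows: "assuming the estimated total counts per day is mean (SD) 275,400 (101,600) minutes". The last word of that quote is a unit slip; the figures are counts/day. For the comparison on each factor the section adds: "This equates to 92 participants per arm of the study".

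The Statistical analysis section first defines the accelerometer outcomes: total counts/day averaged over the measurement period, minutes/day by intensity, numbers of 5- and 10-minute bouts, and the proportion reaching 30 minutes/day. The same paragraph ends with the model: "Generalized linear model (Poisson distribution or Negative Binomial distribution) as appropriate will be used", the results to be given as rate ratios with 95% confidence intervals. The sentence is not labelled as the primary model and is not tied to one outcome, but no other between-group model is named for accelerometer data. The section gives no rule for choosing between the two distributions, no scale parameter and no robust variance.

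**The concern.** A Poisson model fixes the variance of each observation at its mean. Average counts/day from an accelerometer are a device-scaled quantity that varies greatly between people, and the plan's own SD shows it. One of the two listed models therefore assumes a variance that the sample size section contradicts. If it were fitted with its default standard errors, chance differences between arms would almost always be declared significant, in a study meant to show proof of principle and to inform a larger trial.

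The lesser issue is the effect measure. The target is an absolute difference in counts/day, and the Discussion also interprets counts on the absolute scale, but the model reports only a ratio. The result could not be read directly against the 30,000 on which the trial was sized.

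**Working it through.** **Inputs.** Mean 275,400, SD 101,600, target difference 30,000 counts/day and 92 per arm, all from the sample size section. A two-sided 5% test is assumed, since sidedness is not stated.

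**The plan's own sample size.** The two-group formula gives 2 × (1.960 + 0.842)² × (101,600/30,000)² ≈ 2 × 90.0 ≈ 180, rounded up to 181 per arm. The stated 92 does not reproduce without something unstated, such as a baseline correlation of about 0.70 in a baseline-adjusted analysis. That is a separate matter and carries no weight here. I use 92 only as the planned arm size; the 194-fold ratio and the 99% below do not depend on it.

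**Step 1: Poisson variance against the planning variance.**
- SD implied by Poisson: √275,400 = 524.8
- Planned SD: 101,600
- Variance/mean: 101,600² / 275,400 = 37,482
- Ratio of standard errors: √37,482 = 193.6

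The ratio applies to daily averages. On 7-day totals, taking 7 × SD, it would be 7 × 101,600 / √(7 × 275,400) ≈ 512. The apparent precision depends on the unit chosen, which is itself a sign that these are not Poisson events.

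**Step 2: standard errors at 92 per arm.**

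| Quantity | Model-based Poisson | Planning SD |
|---|---|---|
| SE of mean difference | √(2 × 275,400/92) = 77 | 101,600 × √(2/92) = 14,980 |
| SE of log rate ratio | √(2/(92 × 275,400)) = 0.00028 | (101,600/275,400) × √(2/92) = 0.054 |
| 95% CI half-width for the ratio | about 0.06% | about 11% |

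With the Poisson error, a difference of 1.96 × 77.4 ≈ 152 counts/day would be significant. The Discussion equates 100,000 counts with about 30 minutes (1,800 seconds) of brisk walking, so 152 counts is 152/100,000 × 1,800 ≈ 2.7 seconds.

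**Step 3: false-positive rate with unscaled, model-based Poisson errors.** 2 × [1 − Φ(1.96/193.6)] = 0.992. Simulated null trials agree: 99.3% (20,000 trials, gamma counts) and 99.6% (500 trials, gamma-Poisson counts), both at 92 per arm.

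**Step 4: the alternatives.** Negative Binomial dispersion matching the planning moments is (101,600² − 275,400)/275,400² = 0.136. In the 500 null trials, Negative Binomial with that dispersion rejected 5.8%, Poisson with robust errors 5.8%, and a t-test 5.2%. With 500 trials the Monte Carlo SE at 5% is √(0.05 × 0.95/500) ≈ 1 percentage point, so all three are compatible with 5%. A scaled Poisson was not simulated, but scaling multiplies the SE by the root of the variance/mean ratio, which restores 77.4 × 193.6 ≈ 14,980.

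**Step 5: the effect scale.** (275,400 + 30,000)/275,400 = 1.109. This ratio appears nowhere in the article.

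**The case against.** The strongest reply is that the plan does not choose Poisson. The as-appropriate qualifier and the Negative Binomial option are there, Negative Binomial is the usual answer to over-dispersion, and any dispersion check would reject Poisson at a variance/mean ratio near 37,500. This stands. A reader might infer that the trial is committed to an analysis with a type I error near 100%; the text does not support that. The 99% needs two conditions: that Poisson is picked, and that its errors are left unscaled and model-based. A condensed article may leave the variance estimator and the selection rule to a fuller document, so their absence is not the complaint. What remains is that the article positively lists, for total counts, a model that its own sample size paragraph contradicts.

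The sentence also closes a paragraph covering several outcomes, and a count model is natural for numbers of bouts. This stands too, so Poisson-type models need not be struck everywhere.

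On the rate ratio, a reader might infer that the analysis tests the wrong hypothesis. It does not: in an unadjusted two-group comparison, ratio = 1 and difference = 0 are the same null. Converting the target takes one division, and the section says activity data will be presented as counts/day. This part concerns interpretation only.

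The later sentence on change from baseline does not supply the missing model. It follows the clinical and biochemical variables and names no method. If it did cover counts, a change can be negative, which neither listed distribution allows.

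**Conclusion.** The point holds as a permitted, not mandated, error. For total counts/day, the plan's mean and SD rule out Poisson with model-based standard errors: they would be about 194 times too small, with a false-positive rate near 99%. Negative Binomial, or Poisson with robust or scaled variance, would hold about 5 to 6%. These figures assume that the planning SD describes between-person variation in daily averages, that it is the same in both arms, and that the test is two-sided at 5%.

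The rate ratio is a smaller matter: the null is valid, but the result is not on the scale of the 30,000 target. For minutes/day no size can be given, because the article states no mean or SD for them; the same safeguard is advisable.

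This should be fixed, but it is not fatal, because a workable model is already listed.

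**What to change.** State in the Statistical analysis section that total counts/day and minutes/day will not be analysed with unscaled, model-based Poisson errors.

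For the primary outcome, regress follow-up mean counts/day on both randomised factors and baseline counts/day in a linear model with robust standard errors. Report the difference in counts/day for each factor with its 95% CI, and read it against 30,000. A Negative Binomial or gamma log-link rate ratio may be kept as supportive. Count models may stay for numbers of bouts, provided over-dispersion is allowed for.

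The cost is one paragraph of wording. Baseline and follow-up accelerometer data are already collected, so there is no extra measurement and no burden on participants.
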